### Participant timeline

If eligible, subjects are scheduled for the following study visits (Fig. 1). Patients undergo invasive coronary angiography with PCI as per normal clinical care, but they will also undergo IVUS to provide greyscale and virtual histology of all major coronary arteries. Patients with suitable coronary anatomy will be invited to have invasive assessment of coronary and microvascular physiology under adenosine-induced hyperaemia (using a ComboWire; Volcano Corp., Rancho Cordova, CA, USA).

Four weeks later, subjects will re-attend the cardiology department, at which time a full history and physical examination will be performed and inclusion criteria confirmed. Assessments will include a 12-lead electrocardiogram, as well as blood tests (fasted) for blood count and biochemistry (renal, liver, lipid, glycaemic and thyroid profiles) and high-sensitivity C-reactive protein (hs-CRP) and homocysteine levels. Screening blood tests for disorders which may exclude patients from the study will be drawn as indicated (e.g., serum hepatitis B surface antigen, hepatitis C antibody, and HIV testing if prompted by history). Additionally, an aliquot of blood will be taken for measurement of circulating monocyte-platelet aggregates (MPAs, a highly sensitive and reproducible index of degree of platelet activation) by flow cytometry. In the case of women of childbearing potential, pregnancy will be excluded by performing a pregnancy test on a spot urine. Once eligibility has been confirmed, ^13^N-ammonia PET-CT cardiac scans will be obtained at rest and during adenosine-induced hyperaemia to measure CFR. The CT scan will be obtained prior to the PET scan for attenuation correction at rest and stress, and prior to the rest scan, the CT scan will also be used to measure calcium score.

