A secondary outcome is the change in the magnitude of the BEW, a key component of the coronary wave profile, with maximal hyperaemia. From previous work, we expect the magnitude of the BEW to increase 40% with adenosine induced maximal hyperaemia in patients with CAD. Unpublished data from the host centre suggest that in patients without CAD, the BEW can increase a further 14%. Assuming an α error probability of 0.05 (two-tailed), power 0.80 and allocation ratio 2:1 (active drug to placebo), power calculation (using G*Power 3.1.3 software) indicates that we would need 26 subjects in the active and 13 subjects in the placebo group. The BEW measurement has a standard deviation of 21%, as such we will need to recruit 57 patients in total to undergo ComboWire assessment as part of their invasive protocol.

A full description of the statistical analysis plan is beyond the scope of this protocol, and will be published separately. In summary, the primary analysis will be an intention to treat analysis. An analysis of covariance model will be used to obtain an estimate for the mean difference in total CFR between the two treatment groups including covariates for baseline CFR. The estimated treatment effect will be reported with 95% confidence intervals and corresponding *p* value.

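### The backward expansion wave (BEW) sample size does not follow from its own inputs: 39 and then 57 patients are given for the same 80% power, and neither is reproduced

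*Protocol article*

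**What the plan says.** The calculation is in the Protocol article, Statistics and sample size calculation.

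- Expected response: "we expect the magnitude of the BEW to increase 40% with adenosine induced maximal hyperaemia in patients with CAD". For the contrast, unpublished host-centre data are said to suggest that "in patients without CAD, the BEW can increase a further 14" per cent.
- Error rates and allocation: "Assuming an α error probability of 0.05 (two-tailed), power 0.80 and allocation ratio 2:1 (active drug to placebo").
- Result: the software "indicates that we would need 26 subjects in the active and 13 subjects in the placebo group", a total of 39.
- Next sentence: "The BEW measurement has a standard deviation of 21%, as such we will need to recruit 57 patients in total to undergo ComboWire assessment".

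For BEW the section states no standardised effect size, attrition rate or baseline correlation. The endpoint under Outcome measurements is the change in BEW magnitude over 24 weeks. Under Participant timeline, "Patients with suitable coronary anatomy will be invited to have invasive assessment of coronary and microvascular physiology", so the measurement is made in an invited subset.

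**The concern.** Two totals, 39 and 57, are attached to one power statement. The only link between them is the SD, which appears after the power calculation has reported its answer. A two-group comparison of means cannot be sized without an SD or a standardised effect. So either the 39 already used some unstated SD, or the 57 was reached by a step that is not a power calculation.

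At stake is what the ComboWire subset can show. BEW is a named secondary endpoint, it appears in the abstract, and it requires an extra invasive measurement that is repeated at week 24. If the 80% is not what 57 patients deliver, readers will misjudge how informative a null BEW result is.

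**Working it through.** **Inputs** (all from Statistics and sample size calculation): two-sided α = 0.05; power 0.80; allocation 2:1; reference increase 40%; further increase 14%; SD 21%; printed totals 26 + 13 = 39, and 57 (38:19 at 2:1).

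**Method.** Two-sample t test. With n₁ active and n₂ placebo, the noncentrality is λ = d·√(n₁n₂/(n₁+n₂)). Power is the probability that a noncentral t with n₁+n₂−2 degrees of freedom falls outside ± the two-sided 5% critical value.

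**Check on the protocol's other calculation.** For coronary flow reserve the article gives d = 0.7 and 51 + 25. Here λ = 0.7 × √(51×25/76) = 2.87 and power = 0.808. The method agrees with that calculation, so the mismatch below is specific to BEW.

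**Trying to reproduce 39 and 57.** Solving for the effect that gives 80% power:
- 26:13 needs d = 0.98. For a 14-point difference that implies an SD of 14/0.977 = 14.3, not 21. At exact 2:1, 26:13 is also the answer for d = 1.0 (power 0.818, against 0.785 at 24:12), which implies SD 14.
- 38:19 needs d = 0.80. That implies an SD of 14/0.801 = 17.5 for 14 points, or a difference of 0.801 × 21 = 16.8 points at SD 21.

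The two totals therefore imply two different effect sizes, and neither equals 14/21.

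**Reading A: 14% and 21% on the same scale.** d = 14/21 = 0.667.

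| Active:placebo | Total | λ | Power |
|---|---|---|---|
| 26:13 | 39 | 1.96 | 0.481 |
| 38:19 | 57 | 2.37 | 0.645 |
| 55:27 | 82 | 2.84 | 0.800 |
| 56:28 (exact 2:1) | 84 | 2.88 | 0.812 |

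The normal approximation gives n₂ = 1.5 × (1.960 + 0.842)²/0.667² = 26.5, rounded up to 27, hence 54:27 = 81. It gives 66% power for 57 and 50% for 39.

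**Reading B: 14% multiplicative.** 1.40 × 14 = 19.6 points; d = 19.6/21 = 0.933.

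| Active:placebo | Total | λ | Power |
|---|---|---|---|
| 26:13 | 39 | 2.75 | 0.763 |
| 28:14 | 42 | 2.85 | 0.795 |
| 30:15 | 45 | 2.95 | 0.823 |
| 38:19 | 57 | 3.32 | 0.904 |

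At exact 2:1, 45 patients are needed. That is neither 39 nor 57.

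**Other routes, d = 0.667** (normal approximation to t test):
- One-sided at 2:1: 63 to 66.
- Two-sided at 1:1: 72 to 74.
- One-sided at 1:1: 56 to 58. This brackets 57 but contradicts the stated two-tailed test and 2:1 ratio.
- Attrition: 1 − 39/57 = 31.6% loss would be needed. None is stated, and the text attributes the step to the SD.
- Baseline adjustment: reducing 84 to 57 requires 1 − ρ² = 57/84, so ρ ≈ 0.57. The article describes analysis of covariance for coronary flow reserve only.

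**The case against.** The strongest reply is that the article never calls the 14% percentage points. It also does not say whether the 21% is the SD of a single measurement, of the rise with hyperaemia, or of the 24-week change that forms the endpoint. On Reading B, 57 patients have about 90% power. This stands. A reader might infer that the trial is simply underpowered for BEW, or that neither total delivers 80%. The document supports that only if the 14% and the 21% share a scale. Reading B still fails to reproduce either printed total, and it sets a difference rescaled by 1.40 against an SD that has not been rescaled.

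A reader might also infer how 57 arose, since 39 × 1.21² = 57.1 looks like the SD used as an inflation percentage. Nothing in the article shows that step. It may be coincidence, and the point does not need it.

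Nor does the article fix 57 as a ceiling. It already invites patients with suitable anatomy, and if all 90 (60:30) were measured, power on Reading A would be about 84%. That is an upper bound, because anatomy and consent limit uptake.

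Finally, BEW is one of three secondary endpoints and does not drive the primary calculation or the total of 90. That limits the severity. It does not make the printed figures right.

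**Conclusion.** The BEW sample size is wrong as written. One power statement carries two totals, the SD enters after the calculation it should have informed, and I found no reading consistent with the stated two-tailed 2:1 design that yields either total, let alone both.

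The size of the error depends on an undefined scale. On the natural same-scale reading, 57 patients give about 64% power for 14 points at SD 21, a shortfall of about 16 percentage points, and 82 to 84 would be needed. On the multiplicative reading, 57 is more than enough. The range of 64% to 90% assumes complete repeat measurements, an unadjusted t test, and 21% as the SD of whatever is analysed. Grade: should-fix. The primary outcome is unaffected.

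**What to change.** 1. Delete the 26/13 figure.
2. State the assumed between-group difference and its scale (percentage points or relative), the SD of the 24-week change that will be analysed, and any allowance for missing repeat ComboWire studies. Then rerun the calculation once from those inputs.
3. Keep the target of 57 and state the power it delivers. If the same-scale reading is confirmed, that is about 64% for a 14-point difference at SD 21, with 80% power from about 16.8 points. If another scale or SD was meant, print the figure that follows from it.
4. Report BEW as an estimated difference with its 95% CI, so that a non-significant result is read against its precision.

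The cost is a wording change in the protocol and analysis plan. Recruitment, the total of 90 and the primary analysis stay as they are. On the same-scale reading the stated BEW power becomes less favourable.

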### Data collection

#### Electronic case report form

Data are captured in an eCRF which is provided, maintained and stored by KHP-CTO in London, UK. The eCRFs are a component of the custom-designed, trial-specific database built using the InferMed MACRO application, version 4.0 (InferMed/Elsevier, London, UK). Clinical data for the trial are generated by clinical assessments, diagnostic tests, laboratory tests and interviews with the patient during study visits. Source data take the form of patient medical records, hospital records, hospital letters/communications, laboratory reports and so forth. These data are entered into the MACRO application by research staff at the trial site associated with the CICADA study. Privacy of the patients is guaranteed; stored data and materials will be identifiable to the person only by a sequentially assigned subject number. The eCRF is designed in accordance with the requirements of the study protocol and complies with regulatory requirements. Access to the eCRF is password-protected, and the password is given only to site personnel. Data generated throughout the study are monitored, and the eCRFs are checked against the subject records for accuracy. Following completion of the eCRFs, the data are checked electronically for consistency and plausibility by pre-defined range checks. If necessary, automatic queries are generated for questionable data.

#### Data quality control

The clinical research associate and the investigators meet frequently to review study progress and procedures and to discuss any AEs or dropouts. Furthermore, a data monitoring committee has been established to safeguard the interests of the trial’s participants and to monitor the data collected in the trial. The data monitoring committee will meet prior to the start of the study and 6–12 months after the start of the study. The data monitoring committee may also meet on an ad hoc basis should the need arise. The data collection, management, analysis and interpretation, as well as production of publications, are independent of the funding bodies and other competing interests. The trial results will be disseminated via journal publication and conference presentation without exposing the identity of the trial subjects.

### Monitoring

Monitoring is undertaken per good clinical practice guidelines and the study monitoring plan. The study monitor is suitably trained, qualified and experienced to perform this task. Data are evaluated for compliance with the protocol and accuracy in relation to source documents. The following data are assessed:Written informed consentFlowchart filled in for included and excluded subjectsTrial progressPrimary and secondary outcome collectionSAEsDrug accountability of the study treatment

## Discussion

Atherosclerosis is the primary cause of mortality and morbidity in the Western world. Its pathophysiology is not fully understood, but both hyperlipidaemia and inflammation represent central pillars to both atherogenesis and plaque destabilisation. Recent advances point to a contributory role of neutrophils during this process, which offers a novel therapeutic target that could improve outcomes in patients with CAD.

Our study is focused on cardiovascular surrogate parameters, such as CFR function, which cannot replace outcome trials but can provide insights into the potential mechanisms of the cardiovascular effects of CXCR2 inhibition. Moreover, currently ongoing trials are not specifically focused on modulation of neutrophil activity as a target of intervention. We therefore believe that our study will contribute to a better understanding of the role of neutrophil-mediated inflammation in CAD.

## Trial status

Recruitment is ongoing.

## Abbreviations

AE: Adverse event
APV: Average peak velocity
ARSAC: Administration of Radioactive Substances Advisory Committee
BEW: Backward expansion wave
CAD: Coronary artery disease
CICADA: CXCR2 Inhibition – a novel approach to treating CoronAry heart DiseAse
CFR: Coronary flow reserve
CRP: C-reactive protein
CSA: Cross-sectional area
CT: Computed tomography
CXCL: Chemokine (C-X-C motif) ligand
CXCR2: Cysteine-X-cysteine chemokine receptor 2
ECG: Electrocardiogram
eCRF: Electronic case report form
EDTA: Ethylenediaminetetraacetic acid
ESMS: Emergency Scientific and Medical Services
hMR: Hyperaemic microvascular resistance
hs-CRP: High-sensitivity C-reactive protein
IL-8: Interleukin-8
IVUS: Intravascular ultrasound
KHP-CTO: King’s Health Partners Clinical Trials Office
LDL: Low-density lipoprotein
LPS: Lipopolysaccharide
MHRA: Medicines and Healthcare products Regulatory Agency
MI: Myocardial infarction
MPA: Monocyte-platelet aggregate
MPR: Myocardial perfusion reserve
PCI: Percutaneous coronary intervention
P_d_: Distal coronary arterial pressure
PET: Positron emission tomography
SAE: Serious adverse event
SPIRIT: Standard Protocol Items: Recommendations for Interventional Trials
SUSAR: Suspected unexpected serious adverse reaction
VH-IVUS: Virtual histology intravascular ultrasound
WIA: Wave intensity analysis
